### Sample size

A power analysis for logistic regression was conducted using G * Power version 3.1 (Faul *et al.*, 2007). Considering an effect size (odds ratio) of 0.30, a power of .80, and an alpha of .05, a total sample size of 292 patients will be required. The effect size was calculated for a 10% difference between the control condition and experimental condition. Seven-day PPA was estimated to be 5% in the control condition and 15% in the experimental condition.

Assuming that patients are nested within general practices with an average cluster size of five patients, a total sample size of 300 patients will be required. Based on earlier smoking cessation studies in general practices, intra-cluster correlation (ICC) was set at .01. We will aim to recruit 60 PNs that need to recruit an average of 10 patients each. Considering a dropout rate of 50%, there will be 5 patients per GP practice that filled out the baseline questionnaire, totaling 300 patients. In order to account for drop out at six months follow-up, multiple imputations will be conducted by applying Multivariate Imputation via Chained Equations (MICE) in R (Buuren and Groothuis-Oudshoorn, 2010; Blankers *et al.*, 2015).

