### Study design

The aim is to conduct a multi-site two-group parallel randomized controlled trial involving an experimental condition and a control condition. Patients in the control condition will receive care as usual, which usually includes at least a mandatory brief smoking cessation advice and can be supplemented with counseling based on an evidence-based health counseling protocol similar to 5-A’s(Ask, Advise, Assess, Assist, and Arrange) Tobacco Cessation Guideline (Fiore *et al.*, 2000) as also described in the Dutch guidelines for smoking cessation (Chavannes *et al.*, 2017) and previous studies in the GP setting (Pieterse *et al.*, 2001; de Ruijter *et al.*, 2016) in the way the individual PN sees fit. In addition to the usual care, patients in the experimental condition will receive guidance and referral by the PN in accordance with the referral aid in order to select an EBSCI that fits their needs and preferences, which acts as an expansion on the Assist and Arrange steps from the 5-A’s protocol (Fiore *et al.*, 2000). The chosen EBSCI can either be administered by the PN (i.e., face-to-face counseling) or coordinated by the PN (e.g., eHealth, telephone counseling).

Randomization will occur on a practice level to prevent bias between the PN level or the patients level. General practices will be randomly allocated to either the control condition or the experimental condition in a 1:1 ratio. Randomization will take place via a random number generator that creates a string of numbers (1 = control condition, 2 = experimental condition), which will be allocated to general practices in order of registration. Patients are allocated based on their GP practice allocation. By allocation on the practice level, PNs cannot accidentally bias patients from the control group with information intended for the experimental group. As PNs from the experimental condition are provided with an intervention and PNs from the control condition are only asked to provide care as usual, blinding of the PNs is impossible. Patients will be semi-blinded, as they are unaware of the procedure of any other group than the one they attend.

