Patients have to answer two questionnaires – at baseline and follow-up. This can be done on paper or online. Patients receive a link to the questionnaire or a paper version after they have been registered by the PN. The follow-up measurement will take place six months after the baseline questionnaire has been answered. The study design is illustrated in Figure 1.

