### Data analysis

All analyses will be performed following the intention-to-treat principle (Schulz *et al.*, 2010). To account for missing observations in the 6-month follow-up questionnaire, multiple imputations will be conducted by applying MICE in R (Buuren and Groothuis-Oudshoorn, 2010; Blankers *et al.*, 2015).

First, descriptive analyses will be conducted to describe the sample characteristics. Second, logistic regression will be used to analyze attrition, including baseline factors and conditions as predictors. Third, if sample size allows, multilevel logistic regression analyses will be performed to assess differences between conditions in 7-day PPA, 24-hour PPA, and 3-month prolonged abstinence. Fourth, analyses of variance will be performed to test for differences in decisional conflict and appreciation of the intervention materials between conditions.

The economic evaluation will involve the performance of a combination of a cost-effectiveness analysis (CEA) and a cost–utility analysis (CUA) of data collected during the baseline and 6-month follow-up measurement (see quality of life and healthcare costs). In a CEA, the effects are presented in clinical outcomes (here additional quitters). In the CEA, the incremental cost-effectiveness ratio (ICER) will be expressed as the incremental costs per additional quitter (measured as six months PPA). The primary outcomes measure for the CUA will be QALYs, measured via EuroQol (Janssen *et al.*, 2013) and ICECAP (Al-Janabi *et al.*, 2012). The economic evaluation will be performed from a healthcare and societal perspective implying that all relevant costs and outcomes will be considered. Intervention costs, healthcare costs, patient, and family costs (in a subsample), and costs outside the healthcare sector will be assessed.

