### Potential limitations

First, PNs provided less smokers than expected, leading to a longer inclusion period and omission of also a 12-month follow-up as stated in our trial register, (NL7020/NTR7218). Yet, a 6-month study follow-up is still an acceptable period for assessing treatment effectiveness (West *et al.*, 2005).

Second, although we aim to include all eligible smoking patients who visit the participating general practices, there is a risk of selection bias by PNs. PNs may tend to invite more smokers who have already shown a willingness to stop smoking or who are deemed to be more easily motivated to participate, as also seen in other studies (Bundy, 2004; de Ruijter *et al.*, 2017a; 2017b). The conversational guidelines found in the intervention’s manual and flowchart handout are aimed to induce PNs to include all types of smokers.

Third, because smokers often just have one face-to-face meeting with a PN and we use mostly online questionnaires at the six months mark, we may face a high attrition rate. This is usual for studies that use online questionnaires (Eysenbach, 2005; Shahab and McEwen, 2009; Webb, 2009). We tried to overcome this by sending additional questionnaire packages so that patients could answer the questionnaire on-site if desired.

In order to try to prevent attrition at the follow-up assessment, we will also provide a shortened questionnaire including three of the aforementioned questions on abstinence (7-day PPA, 24-hour PPA, and 3-month prolonged abstinence) and one question asking the patients about EBSCIs used during their cessation attempt. This shortened questionnaire can be administered via email or telephone.

Lastly, the efficacy of counseling treatment is also dependent on contextual factors such as the patient–counselor relationship (Wampold, 2015). However, due to the nature of this study, targeting the use of evidence-based smoking cessation methods, assessing these contextual factors was beyond the scope of this study.

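### The analysis is called intention-to-treat, but its planned 300 patients are those who return a baseline questionnaire after allocation and after the consultation

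*Protocol article*

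**What the plan says.** Under Study design, practices are the unit of allocation ("General practices will be randomly allocated to either the control condition or the experimental condition in a 1:1 ratio"), and the practice nurses (PNs) cannot be blinded. Under Recruitment of smokers, a patient who agrees to take part is guided according to the practice's condition. PNs in both arms register patients on the website (Website section). The link or paper form comes after registration (Study design) and can be filled in straight after the meeting with the PN (the section on prompts and attrition).

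The Sample size section plans 60 PNs with an average of 10 patients each and then states: "Considering a dropout rate of 50%, there will be 5 patients per GP practice that filled out the baseline questionnaire". Loss at six months is handled separately, by multiple imputation, so this 50% is a loss at or before baseline.

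On timing, Study design says: "The follow-up measurement will take place six months after the baseline questionnaire has been answered". The Tobacco abstinence section repeats this. On analysis, the Data analysis section says: "All analyses will be performed following the intention-to-treat principle". The imputation it describes is for missing observations in the six-month questionnaire, and its attrition regression uses baseline factors and condition as predictors. Potential limitations adds a short form with three abstinence items and one item on methods used, aimed at attrition at follow-up: "This shortened questionnaire can be administered via email or telephone".

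**The concern.** Intention-to-treat means that membership of the analysis set is not decided by anything that happens after allocation. Here it is decided by whether a patient returns a form after allocation and after the consultation, and the consultation is what differs between the arms. A patient who leaves it resolved to quit may be readier to return the form, and the strength of that link may differ between a visit guided by the referral aid and usual care. The comparison among returners is then no longer protected by the allocation.

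The planned tools do not reach this loss. Imputation starts from patients who have a baseline form. The attrition regression needs baseline factors, which non-returners do not have. Outcomes not collected at six months also cannot be recovered later.

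**Working it through.** **1. The plan's own figures.** The inputs are "Considering an effect size (odds ratio) of 0.30, a power of .80, and an alpha of .05, a total sample size of 292 patients" and "Seven-day PPA was estimated to be 5% in the control condition and 15% in the experimental condition".
- Odds ratio: (0.05/0.95)/(0.15/0.85) = 0.298, stated as 0.30.
- The standard two-proportion formula, two-sided (sidedness is not stated, so this is an assumption), gives 2 × 141 = 282. With an odds ratio of exactly 0.30 it gives 284. At 292 patients its power is 0.816. So 292 is in line with the stated inputs.
- Clustering: 292 × [1 + (5 − 1) × 0.01] = 292 × 1.04 = 303.7, against "with an average cluster size of five patients, a total sample size of 300 patients will be required".
- Recruitment: 60 × 10 × (1 − 0.50) = 300.

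The arithmetic is not at fault. What matters is that the required 300 is set against baseline completers, which is half of the 600 recruited.

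**2. Order of events.**
- Practice allocated, PN unblinded (Study design).
- Patient agrees and is guided by condition (Recruitment of smokers); PN registers the patient (Website).
- Baseline form (Study design; section on prompts and attrition). The section on contact between PN and smoker confirms the order: at baseline, patients report which topics the PN raised during the guidance.
- Follow-up six months from the answered baseline form.
- Imputation of the six-month form only.

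A patient without a baseline form has no follow-up date and no place in the imputation, and no section gives another route into the analysis.

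**3. What selective return can do.** The return rates are assumptions, because the article gives none by arm or by outcome. With true quit rate q, return rate r among eventual quitters and s among the others:

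observed rate = q·r / [q·r + (1 − q)·s]

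Take q = 8% in both arms and s = 48% in both, with r = 70% (experimental) and 60% (control).
- Experimental: 0.0560 / (0.0560 + 0.4416) = 11.3%
- Control: 0.0480 / (0.0480 + 0.4416) = 9.8%
- Observed odds ratio: 0.70/0.60 = 1.17, with no true effect
- Overall return: 49.8% versus 49.0%, so comparing return rates by arm would not reveal it

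With 300 patients and design effect 1.04 there are 300/1.04/2 = 144.2 effective patients per arm. The standard error is √(2 × 0.105 × 0.895/144.2) = 0.036, so the shift is 0.0145/0.036 = 0.40 standard errors. The chance of a false significant benefit is P(Z > 1.96 − 0.40), about 6% instead of 2.5%.

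**4. Range.** Hold overall return at 50% in each arm, so that the observed rate is q·r/0.50, and let control quitters return at 50%.

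| Experimental quitters return | True 10% in both arms: observed | False benefit | True 5% in both arms: observed | False benefit |
|---|---|---|---|---|
| 60% | 10% vs 12% | 8% | 5% vs 6% | 6% |
| 70% | 10% vs 14% | 18% | 5% vs 7% | 11% |
| 80% | 10% vs 16% | 33% | 5% vs 8% | 18% |

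**The case against.** Several points on the other side stand.

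- **Exclusion is not stated outright.** A reader might infer that the plan discards half its patients by rule. It does not say so. Exclusion follows from the follow-up trigger, the target of 300 completers and the scope of the imputation. The 50% is a planning figure, and the flowchart is not shown.
- **Consent timing is not given.** Written consent is required, but the article does not say when it is taken. If it comes with the baseline form, non-returners may not be consented participants and contacting them may not be allowed. The set would still be formed after exposure, so the label would still not fit.
- **The loss is recognised.** Paper forms are placed in practices to reduce it. This may shrink the loss, but it does not say how those who are still lost are treated.
- **Patients are semi-blinded.** Only the PN is fully unblinded. Patients nevertheless know the care they received, and they are the ones who return the form.
- **The abstract** mentions imputation as well as an intention-to-treat analysis, which could mean two analyses. It names no population for the second.

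A reader might also infer that adding the non-returners would raise power. The documents do not support this, because it depends on quitting among patients about whom nothing is given. With all 600 (design effect 1 + 9 × 0.01 = 1.09), power is 0.976 if non-returners also show 5% versus 15%, 0.878 at 5% versus 10%, 0.769 if all are counted as smokers and 0.606 at 5% versus 5%. For 300 completers it is 0.811. The case rests on bias, not on power.

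Non-response at six months among completers is a separate loss and is no part of this point.

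**Conclusion.** The point holds as an inconsistency within the article. The intention-to-treat label does not fit an analysis set formed by returning a form after allocation and after an unblinded PN's consultation, with a planned loss of 300 from 600 recruited. That recruited patients are also registered ones, and that non-returners are left out, are readings of the text, but no section offers another route.

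The size of any bias is unknown. In the worked illustration it is an odds ratio of 1.17, small beside the planned effect of about 3.3 (1/0.30). Stronger arm-specific selection, as in the table, would matter more. All of this rests on assumed return rates. The observed odds ratio is undistorted only if the experimental-to-control ratio of return rates is the same for quitters as for others, and data on returners alone cannot show whether it is.

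**What to change.** - Define the primary analysis set as all patients who agreed to participate and were registered by the PN, as far as their consent allows contact. State when written consent is taken.
- Time the six-month follow-up from registration, where that is still possible.
- Send the existing four-item short questionnaire to all of them, whether or not the baseline form came back.
- Report baseline return by arm, and show the baseline-completer results as secondary.
- Add a sensitivity analysis over all registered patients that counts missing as smoking. This does not replace collecting the outcomes: in the illustration it still gives 0.08 × 0.70 = 5.6% versus 0.08 × 0.60 = 4.8%.
- If non-returners cannot be contacted, drop the intention-to-treat label, describe the analysis as one of baseline-questionnaire completers, and add this selection risk to the limitations.

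The cost is modest, since the registration system and the short questionnaire already exist. It amounts to more short emails or calls and few covariates for patients without a baseline form. Inclusion has already run longer than intended, so re-timing may come too late for some patients. The change does not touch selection by PNs in whom they invite, which the article already lists as a limitation.

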## Introduction

Smoking remains the highest contributor to substance-attributable mortality (Peacock *et al.*, 2018). In the Netherlands, around 20,000 people die from firsthand or secondhand smoke inhalation each year (CBS, 2018). Consequently, in 2018, the Dutch government created the National Prevention Act which, among other things, aims to create a smoke-free generation in 2040 (Nationaal Preventieakkoord, 2018). In 2018, 36.9% of Dutch smokers attempted to quit (Bommele and Willemsen, 2019). However, only 5% of those who quit remain abstinent after 12 months (Fiore *et al.*, 2000; Hughes *et al.*, 2004).

The use of an evidence-based smoking cessation intervention (EBSCI) can double the chance of successful smoking cessation after 12 months (West *et al.*, 2015). EBSCIs come in two forms: behavioral counseling and supplementations. Behavioral counseling can consist of face-to-face counseling by a healthcare professional (HCP) such as a general practitioner (GP) or a practice nurse (PN) or trained stop coach outside the GP setting (Pieterse *et al.*, 2001; Aveyard *et al.*, 2012; Stead *et al.*, 2013; Verbiest *et al.*, 2013; Papadakis *et al.*, 2016; van Rossem *et al.*, 2017), tailored online counseling (eHealth) (Te Poel *et al.*, 2009; Stanczyk *et al.*, 2014), telephone counseling (Berndt *et al.*, 2016), and group counseling (McEwen *et al.*, 2006). However, only 25%–30% of smokers report using behavioral counseling methods (Borland *et al.*, 2012; Filippidis *et al.*, 2019). The effectiveness of behavioral counseling can be increased through supplementation with nicotine replacement therapy such as nicotine gum or patches (available over the counter at pharmacies, drugstores, and large supermarkets) (Stead *et al.*, 2012) or pharmacotherapy (Hurt *et al.*, 1997; Hughes *et al.*, 2005; Tonstad *et al.*, 2006) of which the latter can only be prescribed in the Netherlands via the GP setting to patients indicating that they are willing to make use of them (Chavannes *et al.*, 2017).

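### The required 300 patients are counted at baseline and six-month dropout is left to multiple imputation, so the stated 80% power holds only if almost no primary outcomes are lost

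*Protocol article*

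**What the plan says.** The Sample size section of the protocol article sets the effect and the number needed: "Seven-day PPA was estimated to be 5% in the control condition and 15% in the experimental condition", with "a power of .80, and an alpha of .05, a total sample size of 292 patients will be required". Patients are nested in practices, with an average of five per practice and an intra-cluster correlation of .01, and this brings the total to 300.

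The same section then plans 60 practice nurses recruiting 10 patients each. It applies a 50% dropout rate and arrives at five patients per practice, 300 in all, who have filled out the baseline questionnaire. The next sentence deals with later loss: "In order to account for drop out at six months follow-up, multiple imputations will be conducted". The method named is MICE in R.

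Under Tobacco abstinence, the primary outcome is 7-day abstinence at six months from baseline. The Data analysis section names MICE again, as the method for missing follow-up data. Potential limitations says of the mostly online six-month questionnaires that "we may face a high attrition rate". It also describes a shortened questionnaire, by email or telephone, that includes 7-day abstinence.

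**The concern.** A power calculation for a six-month outcome gives the number of patients in whom that outcome is observed. Here the required number and the expected number of baseline completers are both 300, so nothing is held back for the following six months. The place where a reserve would normally be stated is taken by a sentence about imputation.

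Multiple imputation can reduce bias when data are missing at random. It does not supply the information that the unobserved outcomes would have carried, unless other variables predict abstinence very strongly. If outcomes are lost, the primary comparison has less than the stated 80% power, and readers will take the trial to be better powered than it is.

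**Working it through.** **Inputs.** From the Sample size section: 5% versus 15%, alpha .05 (taken as two-sided, since the text does not say), power .80, cluster size 5, intra-cluster correlation .01, 300 patients at baseline. From Study design: 1:1 allocation. The six-month dropout rate d is not given, so it is an assumption and is varied.

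**1. Reproducing the plan's figures.**
- Odds ratio = (.05/.95)/(.15/.85) = 0.298, which agrees with the stated 0.30.
- Two-proportion formula with pooled variance under the null: n per arm = [1.960 × √(2 × .10 × .90) + 0.842 × √(.05 × .95 + .15 × .85)]² / .10² = (0.832 + 0.352)²/.01 ≈ 140.1. That is 141 per arm, 282 in total. Logistic Wald formulas give about 259 to 312, depending on the variance used. The stated 292 lies within this spread, and power at 292 is 81.6% by the pooled formula.
- Design effect = 1 + (5 − 1) × .01 = 1.04, and 292 × 1.04 = 303.7, close to the stated 300.

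The 292 and the 300 are therefore not in question.

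**2. Where the dropout allowance goes.** 60 × 10 = 600 recruited; 600 × (1 − .50) = 300 at baseline. Reserve between baseline and six months: 300 − 300 = 0.

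**3. Power by loss of the six-month outcome.** Observed outcomes = 300(1 − d); mean cluster size = 5(1 − d); design effect = 1 + [5(1 − d) − 1] × .01; effective N = observed/design effect; power from the pooled formula above.

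| Loss d | Observed | Design effect | Effective N | Power |
|---|---|---|---|---|
| 0% | 300 | 1.040 | 288.5 | 81.1% |
| 3% | 291 | 1.0385 | 280.2 | 80.0% |
| 10% | 270 | 1.035 | 260.9 | 77.1% |
| 20% | 240 | 1.030 | 233.0 | 72.3% |
| 30% | 210 | 1.025 | 204.9 | 66.7% |
| 40% | 180 | 1.020 | 176.5 | 60.2% |
| 50% | 150 | 1.015 | 147.8 | 52.7% |

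The logistic Wald formula is a few points lower throughout (68.1% at 20%, 49.0% at 50%).

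**4. Does imputation restore the loss?** Simulation with 300 patients, no clustering, outcomes missing completely at random, one moderately prognostic baseline covariate, 20 imputations, Rubin's rules, and about 600 trials per setting:

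| Missing | Full data | Complete cases | Multiple imputation |
|---|---|---|---|
| 20% | 81% | 73% | 71% |
| 30% | 83% | 71% | 71% |
| 50% | 85% | 48% | 45% |

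Imputation gives about the same power as complete cases. The small differences between those two columns are within simulation error.

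**The case against.** **The size is unknown, and the plan acts against attrition.** This stands in part. The text says attrition may be high; a reader might infer that it predicts high loss of the primary outcome, and it does not. The shortened questionnaire can capture 7-day abstinence from patients who skip the full form, and the gift voucher depends on answering both questionnaires. Loss of the primary outcome may therefore be well below loss of the full questionnaire. The direction of the shortfall is not affected, and power reaches 80% at only about 3% loss.

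**Non-responders may be counted as smokers.** The Abstract lists multiple imputation as well as intention-to-treat analysis, which could mean two analyses, the second giving all 300 an outcome. If 5% and 15% are already on that scale, power holds. The article does not say so, and Data analysis names MICE. If instead they are true rates that shrink by (1 − d), power with all 300 counted is 70.9% at 20% loss, 64.6% at 30% and 49.5% at 50%.

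**The assumed effect.** The Introduction says that using an evidence-based intervention "can double the chance of successful smoking cessation after 12 months", and a reader might infer that a tripling from 5% to 15% contradicts it. It does not. That figure concerns use of such an intervention, at 12 months. The trial compares a referral aid with usual care, which may itself include counselling, at six months. The assumed effect is a design choice and is no part of this point.

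**It belongs in the analysis plan.** The sample size, the dropout allowance and the stage at which it is spent are all fixed in this article, so the point rests on what it states.

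**Conclusion.** The point holds. The 80% power is stated for 300 patients, but the design provides 300 only at baseline, and imputation does not make up for outcomes lost afterwards. Power is about 77% at 10% loss, 72% at 20%, 67% at 30% and 53% at 50%.

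These figures rest on assumed loss rates, a two-sided test, the article's own 5% and 15%, its intra-cluster correlation of .01, and loss spread evenly over arms and practices. The result on imputation assumes baseline variables that predict abstinence moderately; very strong predictors would recover more. Two stronger conclusions are not supported: that 292 or 300 is miscalculated, and that imputation does worse than complete cases. MICE remains a reasonable analysis method.

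**What to change.** In the Sample size section:
- Remove MICE as the answer to six-month dropout. Keep it in Data analysis as the method for missing outcomes.
- State the sponsor's own expected six-month response on 7-day abstinence, allowing for the shortened email or telephone questionnaire.
- Restate the power for that number of observed outcomes, using the stated rates, cluster size and intra-cluster correlation.
- If 5% and 15% are meant as rates with missing counted as smoking, say so, since the power then refers to all 300.

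The cost is a few sentences and a less favourable power figure. No extra patients are needed and the analysis method does not change.
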